#### 2.4.3. Effectiveness Outcomes

Effectiveness outcomes include women’s depression symptoms (primary), coping behaviours, self-efficacy, perceived support levels, intimate relationship satisfaction, post-abortion personal growth, and abortion-relevant outcomes. Specific measures include:

##### Depression

Changes in women’s depression symptoms will be measured by the Patient Health Questionnaire (PHQ-9) [25]. The nine-item scale will be administered at the initial patient interview and monitor progress. Participants will be asked to rate the severity of their depressive symptoms on a four-point scale (0 = not at all; 1 = several days; 2 = more than half the days; and 3 = nearly every day). The nine items cover symptoms associated with experiencing pleasure, feeling down, and self-esteem. The total score can range from 0 to 27, with higher scores indicating greater severity of depression. The tool has been translated and validated with the Chinese population, showing strong psychometric properties (α = 0.86) [26].

##### Coping Behaviours

The Carver Brief COPE Inventory [27] will be used to measure changes in women’s coping behaviours. This 28-item inventory measures the use of 14 coping behaviours (2 items per strategy). Women are asked to rate how often they adopted each behaviour within the previous 2 weeks on a four-point Likert scale, ranging from 0 (I have not been doing this at all) to 3 (I have been doing this a lot). Coping behaviours are categorised into three dimensions: (1) problem-focused coping (four sub-scales: active coping, use of informational support, positive reframing, and planning); (2) emotion-focused coping (six sub-scales: emotional support, venting, humor, acceptance, religion, self-blame); and (3) dysfunctional-focused coping (four sub-scales: self-distraction, denial, substance use, and behavior disengagement). Brief COPE has been widely utilized in different populations, including women who experienced pregnancy termination for fetal abnormality [28]. The Chinese version of Brief COPE has shown adequate psychometric properties with a Cronbach’s alpha of <0.60 [29,30].

##### Self-Efficacy

The General Self-Efficacy scale (GSE-10) [31] has 10 items measuring optimistic self-beliefs to cope with difficulties in life. Items of GSE were scored on a four-point Likert scale, ranging from 1 (not at all true) to 4 (completely true). Scores range from 10–40 with higher total scores indicating that an individual feels more competent in dealing with stressful encounters. It is valid, reliable and has been translated into more than 30 languages, including Chinese [32]. The internal inconsistency of the Chinese version was 0.91 [32].

##### Perceived Social Support

The abbreviated version of the Medical Outcomes Study Social Support Scale (MOSSS-5) [33] and seven study-specific questions will be used to measure perceptions of support. The MOSSS-5 is a five-item reliable measure of perceived social support. Each item is scored on a five-point Likert scale and the items are summed for a total score ranging from 5−25. Its Chinese version has adequate test–retest reliability (0.89), and internal consistency items ask participants to rate their satisfaction, degree of happiness, feelings of reward, and comfort with their partners. Each question has different response formats. Total scores range from 0 to 21, with higher scores indicating greater satisfaction. The Cronbach’s α reliability of the translated version in Chinese women is 0.88 [34].

##### Post-Abortion Growth

The Post-traumatic Growth Inventory Short Form (PTGI-SF) evaluates personal growth following traumatic, challenging and stressful life circumstances [35]. PTGI-SF comprises 10 items rated on a six-point Likert scale (ranging from 0 to 5), with a total score ranging from 0 to 50. Higher scores indicated higher PTG. The 5 subscales include relating to others, new possibilities, personal strength, spiritual change, and appreciation of life. The Chinese version has acceptable internal consistency with a Cronbach α of 0.86 [36].

##### Abortion Related Outcomes

Abortion related outcomes will be measured according to women’s gestational weeks at abortion, type of abortion, complications, and follow-up-exam attendance.

### 2.5. Sample Size

A formal sample-size calculation is not necessary for research objectives 1 and 2 [20]. For objective 3, G*Power software was used to determine reasonable sample size for the estimation of differences between intervention and control groups. The effect size on depression reported by similar interventions ranged from 0.39 to 1.06 [37,38,39]. G*power indicated a total of 72 participants will be required to detect a 0.39 effect size for depression, two tailed, with alpha at 0.05 and power at 90%. Anticipating a 20% attrition rate, recruitment was set at 90 (45 women per group).

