### 2.10. Protocol Modifications

During the conduction of the trial, if we observe a higher-than-expected drop-out rate at the two-weeks post-abortion follow-up, we will increase the sample size from 90 (calculated on a 20% attrition rate) to 110 (calculated on a 35% attrition rate) to achieve precision for the estimation of the effect size. Paper-based questionnaires will be left for women to fill out on their own. However, if participants express being overwhelmed by the amount of information required, we will conduct an interview during which participants could ask clarifying questions. This approach will minimize missing data and enhance the retention rate.

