## 4. Conclusions

This paper proposes a protocol of a clinical trial to assess the feasibility, acceptability, and potential effects of a comprehensive supportive intervention that was developed to address the psychological health of Chinese women undergoing an abortion. Results will be used to assist intervention refinement and direct a future full-powered trial. Practical experience will be gained throughout the clinical trial, which would also provide evidence for further implementation of the intervention.

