**Effectiveness outcomes**				
Depression	T-0, -1, -2, -3	Primary researcher (T0, 3) and nurse coordinator (T-1, -2); at clinic facilities; face to face (T-0, -1, -2) and by telephone (T-3)	SMD-A	Descriptive statistics *t*-test/Mann–Whitney U test comparing baseline to T-3 *t*-test/Mann–Whitney U test comparing differences between groups at T-3 Linear regression measuring change over time
Perceived support	T-0, -1, -2, -3	As above	MOS-SSS	As above
Intimate relationship	T-0, -1, -2, -3	As above	CSI-4	As above
Coping behaviours	T-0, -2, -3	As above	CBCI	Descriptive statistics *t*-test/Mann–Whitney U test comparing baseline to T-3 of each coping style *t*-test/Mann–Whitney U test comparing differences between groups of each coping style at T-2 and T-3
Self-efficacy	T-0, -2, -3	As above	GSE-10	Descriptive statistics *t*-test/Mann–Whitney U test comparing baseline to T-3 *t*-test/Mann–Whitney U test comparing differences between groups at T-2 and T-3
Post-abortion growth	T-2, -3	As above	PTGI-SF	Descriptive statistics *t*-test/Mann–Whitney U test comparing T-2 to T-3 *t*-test/Mann–Whitney U test comparing differences between groups at T-2 and T-3
Abortion outcomes	T-3	As above	Self-design questions	Descriptive statistics Chi Square test comparing differences between groups at T-3

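### The 72 completers give about 37% power, not 90%, for a between-group effect of 0.39 on depression; the planned two-arm test needs about 280

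*Protocol article*

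**What the plan says.** Section 2.5 exempts objectives 1 and 2 from a formal calculation and makes one for objective 3: "G*Power software was used to determine reasonable sample size for the estimation of differences between intervention and control groups". The effect size comes from earlier work: "The effect size on depression reported by similar interventions ranged from 0.39 to 1.06". The result is that "72 participants will be required to detect a 0.39 effect size for depression, two tailed, with alpha at 0.05 and power at 90"%. Attrition is then added: "Anticipating a 20% attrition rate, recruitment was set at 90 (45 women per group"). Neither the G*Power test nor the effect-size metric is named.

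Section 2 fixes 1:1 allocation, and section 2.4.3 makes depression the primary effectiveness outcome. The Depression row of Table 3 plans a t-test or Mann–Whitney "U test comparing differences between groups at T-3", a baseline to T-3 comparison, and a linear regression for change over time.

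Section 2.10 carries the same base of 72 into a contingency: "we will increase the sample size from 90 (calculated on a 20% attrition rate) to 110 (calculated on a 35% attrition rate"). The Conclusions say the results will "direct a future full-powered trial".

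**The concern.** Section 2.5 gives every input except the test and the metric, and for a comparison of two independent arms those inputs do not lead to 72. A standardised difference of 0.39 is modest, and 36 women per arm is far too few to detect it with 90% power.

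The error affects how the depression result will be read. Readers are told the risk of missing an effect of 0.39 is 10%; for the planned T-3 test it is about 63%. A non-significant result could then be taken as evidence against START. If the true effect is near 0.39, a significant result would have to come from an overestimate, and that estimate would feed the planning of the next trial.

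**Working it through.** **Inputs.** Effect size 0.39, two-sided alpha 0.05, power 90%, total 72, attrition 20%, 45 per group (section 2.5); 1:1 allocation (section 2); between-group t-test or Mann–Whitney at T-3 (Table 3); 110 at 35% attrition (section 2.10). Assumption: 0.39 is a standardised mean difference *d* between arms, since the metric is not stated.

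**1. Where 72 comes from.** Three calculations return it:
- One-sample or paired t-test with *d* = 0.39: noncentrality *d*√n = 0.39 × √72 = 3.31 on 71 df. Power is 90.4% at n = 72 and 89.99% at n = 71, so 72 is the exact answer.
- Two-group F test with 0.39 entered as Cohen's *f*: *d* = 2*f* = 0.78. Power is 90.4% at 36 per arm and 89.6% at 35.
- Repeated-measures interaction, 2 groups and 2 time points, *f* = 0.39/2 = 0.195, assumed correlation 0.5: power is 90.4% at 72 in total and 89.6% at 70. This *f* means a difference in change of 4 × 0.195 = 0.78 SD.

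The first is a within-woman test. The other two compare arms, but at 0.78 SD.

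**2. Sample size for the stated comparison.** Normal approximation, per arm:

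n = 2(z₀.₉₇₅ + z₀.₉₀)² / *d*² = 2(1.960 + 1.282)² / 0.39² ≈ 138.2, so 139.

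With the noncentral t distribution, 139 per arm falls just short (89.97%) and 140 suffices (90.2%): **280 completers**. With 20% attrition, 280/0.8 = **350 recruited**, against 72 and 90 stated. For 80% power the figure is 105 per arm (210 in total).

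**3. Power at *d* = 0.39.** Noncentrality is *d*√(n/2), with 2n − 2 df. At 36 per arm it is 0.39 × √18 = 1.65 against a critical value of 1.994.

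| Analysed per arm | Power |
|---|---|
| 36 (72 completers) | 37.2% |
| 45 (all 90, no attrition) | 44.8% |
| 55 (all 110, no attrition) | 52.7% |

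**4. What 36 per arm can do.** The detectable difference is *d* ≈ 0.77 at 90% power and 0.67 at 80%. The 95% CI half-width is 1.994 × √(2/36) = 0.47 SD.

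**5. Other between-group variants at *d* = 0.39.** One-sided at 90% power needs 228 in total. Reading 72 as the number per arm gives 64% power. Mann–Whitney needs about 294 (280 divided by an efficiency of 0.955, rounded up per arm).

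**6. Attrition steps.** 72/0.8 = 90, as stated. 72/0.65 = 110.8, which rounds up to 111; 110 × 0.65 = 71.5. The contingency therefore only keeps about 72 completers and inherits the low power.

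**The case against.** The strongest reply is that the 37% depends on reading 0.39 as a between-group *d* in an unadjusted T-3 test, and the article names neither the metric nor the test. One route to 72, the repeated-measures interaction, does compare the arms and would fit the planned regression over time. That is fair as to which error was made: it cannot be settled from the text. It does not restore the claim. That route, like the Cohen's *f* route, has 90% power for 0.78 SD. The *f* reading also fits poorly with a two-tailed test, and would turn the cited upper value of 1.06 into *d* = 2.12.

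A second reply is that baseline adjustment raises power; the Discussion mentions adjusting for baseline differences. It does help, but at 36 per arm power is 47% at an assumed baseline-to-follow-up correlation of 0.5 and 63% at 0.7. About 0.86 would be needed for 90%. No correlation is stated, and the T-3 test in Table 3 is unadjusted.

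Third, 0.39 is the bottom of the cited range. At 36 per arm, power is 83% at *d* = 0.70 and 99% at 1.06, so the trial is not weak across that range. This limits the worry about overestimates to true effects near 0.39. But 0.39 is the value for which section 2.5 claims 90%.

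Fourth, this is a feasibility trial described as preliminary. That justifies a small sample, but not an incorrect power figure. The half-participant shortfall at 110 is rounding, and a later fully powered trial could be wanted for other reasons, so that remark is in tension with the power claim but proves nothing by itself.

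**Conclusion.** The stated power is wrong as written. For the between-group comparison that section 2.5 describes and Table 3 plans, 72 completers give about 37% power at *d* = 0.39, and 90% power needs 280, nearly four times as many. This rests on 0.39 being a standardised mean difference between arms and on an unadjusted T-3 test. At assumed correlations of 0.5 to 0.7, baseline adjustment would raise power to 47–63%, still well short of 90%. The size of 90 is defensible for a feasibility trial; the power statement attached to it is not, and it must be corrected because it concerns the primary effectiveness outcome.

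**What to change.** - **Section 2.5:** delete the claim of 90% power at 0.39. Name the test and the effect-size metric. Keep 90 recruited, and state that 72 completers (36 per arm) give about 37% power for *d* = 0.39 and 90% power only for *d* of about 0.77.
- **Objective 3:** make the main result the between-group difference in depression with its 95% CI (expected half-width about 0.47 SD), and say that p > 0.05 will not be read as absence of effect.
- **Section 2.10:** justify 110 by the CI width it preserves at 35% attrition (about 72 completers, so again about 0.47 SD), or correct it to 111.

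The alternative, keeping 90% power at 0.39 with the planned test, would mean 350 recruited, which is out of scale for this trial. The recommended change costs wording and recomputed figures, with no additional participants. The price is a less favourable power statement.

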### 2.6. Recruitment and Consent

When women present at the FPRHC seeking an abortion, they receive a consultation to ensure informed choice and a medical appointment to assess their physical health. If the woman confirms her decision to terminate the pregnancy, she speaks with a nurse to make an appointment for the abortion. As reception nurses have an ongoing relationship with patients and are available during clinic hours, they will screen women based on the inclusion and exclusion criteria. If eligible, the reception nurse will provide a brief explanation about the study and ask women if they are interested in participating. If yes, women will be referred to the primary researcher, who will discuss the study in more depth, answer any questions, and provide the Participant Information and Consent Forms. The potential participant will be given adequate time to read the forms, talk with her support person, and ask questions before deciding to participate or decline. Participants will be assured they can withdraw from the study at any time, and it will not influence their treatment in any way.

### 2.7. Assignment and Blinding

Considering the small sample size, block randomization will be used to reduce bias and ensure an equal balance between the intervention and control groups [40]. A block size of four with six possible balanced combinations of assignment within the block is considered appropriate for this study. The nurse coordinator will generate a random number sequence using Microsoft Excel and place the assignments into sealed envelopes. After informed consent, the primary researcher will open a sequential envelope to determine the group allocation of each participant. Given the nature of the intervention, it is not feasible to blind the participants, intervention providers, and researchers who collect data. To prevent contamination, women in the intervention group will be asked not to share information or materials of the study with other abortion patients before completion of the study.

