## 2. Materials and Methods

The study adopts a two-arm randomized controlled trial design with quantitative and qualitative information collected. Participants will be randomly allocated to receive either the START intervention in addition to standard abortion care or standard abortion care only with a 1:1 allocation rate. The study design is directed by the CONSORT statement and its extensions [20,21] and the Standard Protocol Items: Recommendations for Interventional Trials (SPIRIT) 2013 guideline for protocols of randomized trials [22]. The research activities inconsistent with the real-world clinical practice are outlined in Figure 2.

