### 2.1. Setting

This study will be conducted in the Family Planning and Reproductive Health Centre (FPRHC) of a tertiary hospital in Beijing, China. Participants will be recruited from the outpatient unit of the FPRHC, where abortion-related services are normally provided.

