**Figure 2 ijerph-19-06611-f002:**
[figure not shown]
SPIRIT standard flow diagram.

**Table 1 ijerph-19-06611-t001:** Intervention description according to TIDieR checklist.

TIDieR Item	Intervention Group	Control Group
**1.** **BRIEF NAME**	The START intervention	Standard abortion care
**2.** **WHY**	Based on the Transactional Model of Stress and Coping, the START intervention intends to help women cope with abortion experience by addressing the specific stressors they face in the Chinese context, hence promoting well-being	N/A
**3.** **WHAT-Materials**	Consultation, an information booklet, a WeChat-based public profile page, and a hotline	N/A
**4.** **WHAT-Procedure**	All participants allocated to the intervention group will be offered a 30-min face-to-face consultation. The consultation includes a brief introduction of the public profile page, Q&A, and offering emotional support and information on available coping resources. A printed information booklet will be provided during the consultation. Meanwhile, by scan the QR code, participants will be endowed with unlimited access to the public profile page till the closure of the project. A hotline will also be offered.	(1) prior abortion consultation on informed choice of pregnancy; (2) abortion preparation education on abortion practice, and steps involved; (3) a brief discharge education session on warning signs of potential complications and post-abortion contraception; and (4) a regular 2-week post-abortion appointment to determine the completion of the abortion.
**5.** **WHO PROVIDED**	The consultation, information booklet, and managing the public profile page will be carry out by the primary researcher who is a qualified abortion counsellor. Hotline will be answered by a registered nurse who has more than 10 years clinical experience in abortion care.	Prior abortion consultation and post-abortion exam-by doctors Abortion preparation and discharge education-by nurses
**6.** **HOW**	Consultation (face to face) Information booklet (hard copy) Public profile page (internet) Hotline (telephone)	Face to face
**7.** **WHERE**	Consultation (the consultation room) Information booklet (the consultation room) Public profile page (WeChat based) Hotline (telephone-base)	Health centre facilities

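### A single fixed block of four, with the envelopes opened by the unblinded researcher who also leads consent and delivers START, can make about a third of allocations foreseeable

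*Protocol article*

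**What the plan says.** Section 2 sets two arms, the comparator being "standard abortion care only with a 1:1 allocation rate". Section 2.1 names one centre: "This study will be conducted in the Family Planning and Reproductive Health Centre (FPRHC) of a tertiary hospital in Beijing, China". No stratification is described, so there is one running sequence. On the blocks, Section 2.7 states: "A block size of four with six possible balanced combinations of assignment within the block is considered appropriate for this study". The nurse coordinator makes the list in Excel and fills sealed envelopes.

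The same section says: "After informed consent, the primary researcher will open a sequential envelope to determine the group allocation of each participant". It also says: "Given the nature of the intervention, it is not feasible to blind the participants, intervention providers, and researchers who collect data".

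The primary researcher has several roles around that step:
- **Consent.** Under Section 2.6, reception nurses screen for eligibility, give a brief explanation and ask about interest. If the answer is yes, "women will be referred to the primary researcher, who will discuss the study in more depth" and provides the consent forms.
- **Baseline.** Table 3 has the primary researcher collect depression at T-0, which Section 2.8 places before randomization.
- **Treatment.** Table 1, item 5: "The consultation, information booklet, and managing the public profile page will be carry out by the primary researcher who is a qualified abortion counsellor".

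The Discussion (Section 3) states that randomization, together with adjustment for baseline differences, will protect against selection bias.

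**The concern.** Sealed envelopes hide what is inside the next one. They do not hide what came out of the earlier ones. With a constant block of four at 1:1, the fourth allocation in each block follows from the first three, and the third follows whenever the first two agree. The person best placed to make that deduction is the one who has opened every envelope so far and has treated every woman allocated to START. The same person conducts the consent discussion with the next woman.

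What is at stake is allocation concealment. A researcher who knows the next arm can, without intending to, present the study differently, bring a consent forward or put it off, or carry out the T-0 assessment differently. Blinding is declared infeasible and the primary outcome is self-reported depression, so concealment is one of the few protections against bias still open to the trial. Objective 3 tests preliminary efficacy, and Section 4 says the results will direct a full-powered trial, so feasibility status does not make the point idle.

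**Working it through.** **Inputs.** Allocation 1:1 (Section 2); block size 4, fixed (Section 2.7); one site (Section 2.1); planned N = 90 (Section 2.5), or 110 if attrition is high (Section 2.10). Assumption: the observer knows the block size and all earlier allocations in order.

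**The plan's own figure.** The number of balanced sequences in a block of four is C(4,2) = 6. This agrees with Section 2.7.

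**Certain allocations.** An allocation is certain when one arm has already filled its two places in the block.

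| Sequence | Certain allocations |
|---|---|
| AABB, BBAA | 2 each |
| ABAB, ABBA, BAAB, BABA | 1 each |

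The total is 2×2 + 4×1 = 8 of 6×4 = 24, which is 1/3. By position the probabilities are 0, 0, 1/3 and 1, so each complete block has on average 4/3 certain allocations, and always either 1 or 2.

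- N = 90 is 22 complete blocks plus 2 women, whose positions are never certain. Expected: 22 × 4/3 = 29.3, and 29.3/90 = 32.6%. Range: 22×1 = 22 to 22×2 = 44.
- N = 110 is 27 complete blocks plus 2 women. Expected: 27 × 4/3 = 36.0, and 36.0/110 = 32.7%.

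**Best guess.** The observer guesses the arm with more places left and tosses a coin when they are equal. Success by position:
- 1st: 1/2
- 2nd: 2/3
- 3rd: 1/3×1 + 2/3×1/2 = 2/3
- 4th: 1

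The mean is (1/2 + 2/3 + 2/3 + 1)/4 = 17/24 = 70.8%, against 50% without blocking.

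**Alternatives.** The fixed blocks of 6 and 8 were enumerated in the same way. The varying blocks were simulated (3,000 sequences of 90), with an observer who knows the possible sizes but not where each block ends. The first row gives the exact values for complete blocks of four; simulated at N = 90 they are 32.6% and 70.6%.

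| Scheme | Certain | Best guess correct |
|---|---|---|
| Fixed 4 | 33.3% | 70.8% |
| Fixed 6 | 25% | 41/60 = 68.3% |
| Fixed 8 | 20% | 373/560 = 66.6% |
| Varying 2, 4, 6 | 4.1% | 70.2% |
| Varying 4, 6 | 5.5% | 69.1% |
| Varying 4, 6, 8 | 2.3% | 68.0% |

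Enlarging a fixed block leaves much of the certainty in place; varying the size removes most of it. Neither brings guessing close to 50%.

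**The case against.** **Nurses make the first approach.** Reception nurses apply the criteria and ask about interest before the primary researcher meets the woman. This stands. It rules out the reading that the researcher chooses whom to approach. What remains is the consent discussion, its timing and the T-0 assessment.

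**Recruitment is monitored.** The proportion of eligible women recruited is a feasibility outcome (Section 2.4.1), with a criterion of at least 80% (Section 2.9), so selective refusal would show in a reported figure. This stands in part. With 90 recruited, 90/0.80 = 112.5, so 22 of 112 eligible women could decline and the criterion would still be met. A change in the timing of consent would not show at all.

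**The figure is conditional.** Section 2.7 does not say that the primary researcher is told the block size, and one third is an expectation. This stands, so the condition belongs in the conclusion. Knowledge of the block size within a small study team is plausible, but the article does not establish it. Publication adds little, because the article does not say whether recruitment came first.

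**The remedy hardly changes guessing.** This also stands. Varying blocks takes best-guess success only to 68–70%. That is why the fix also covers the order of steps at the envelope and who opens it.

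**Stronger readings to avoid.**
- A reader might infer that allocation was in fact subverted; nothing in the article shows this.
- Because 90 is not a multiple of four, a reader might count the missing guarantee of 45 per group as a fault. The half block allows at most 46/44, which is trivial, and varying blocks loosens the split further.
- A reader might add that the primary researcher also collects the T-3 outcome. That is a question of unblinded assessment, which Section 2.7 discloses and which block size does not affect.

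**Conclusion.** The concern holds in a conditional form. The article fixes a single block of four in one unstratified, unblinded sequence, and the opening of every envelope lies with the person who leads the consent discussion and delivers START. If that person knows the block size and tracks past openings, an expected 29.3 of 90 allocations (32.6%; possible range 22 to 44) are certain before consent is completed. Without that knowledge and tracking, the figure does not apply.

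The consequence is an avoidable opening for selection at the consent and T-0 stage, and a weaker basis for the Discussion's claim about selection bias. It is not evidence that selection took place. The rule should be changed because the change is cheap and removes most of the certainty; residual guessing would remain.

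**What to change.** 1. Replace the fixed block with randomly varying sizes, for example 4, 6 and 8, and withhold the sizes and their order from the primary researcher. Certain allocations fall from about 33% to about 2%, or to about 4% with sizes 2, 4 and 6.
2. State in Section 2.7 that consent and the T-0 assessment must be complete, and the study ID and time written on the sealed envelope, before it is opened. Section 2.8 already places T-0 before randomization; this makes the order checkable.
3. Where existing staff allow, have someone other than the enrolling researcher open the envelopes. The article names no team member who is clearly free for this, so it is a preference and not a condition.

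**Cost.** A new allocation list and one extra entry per envelope. The final split may be less even: an incomplete last block of up to 8 can leave a difference of at most 4 women, for example 47/43 instead of 45/45.
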